#### Secondary outcomes

Change in symptoms of depression at T3 and T4 when compared to T2 will be assessed using the Patient Health Questionnaire—9 item version (PHQ-9) [48]. Participants will be asked to indicate how often they have been bothered by nine problems over the past 2 weeks. Each item is rated on a 4-point Likert scale ranging from 0 (“not at all”) to 3 (“nearly every day”). Scores are summed such that the potential range is 0–27, with higher scores indicative of greater distress.

Changes in hopelessness at T3 and T4 when compared to T2 will be assessed using the Hopelessness Scale for Children (HSC) [49], a 17-item measure of the occurrence of cognitions related to hopelessness within the past week. Participants rate each item as true or untrue of them; items 1, 3, 4, 5, 6, 7, 11, and 16 are scored as reflecting hopelessness if rated “false” and items 2, 8, 9, 10, 12, 13, 14, 15, and 17 if rated “true”. Higher scores (maximum = 17) reflect greater hopelessness or negative expectations towards the future.

Change in problem-solving ability at T3 and T4 when compared to T2 will be assessed using the Negative Problem Orientation Questionnaire (NPOQ) [50], which contains 12 items assessing dysfunctional attitudes related to problem-solving ability. Items are rated on a 5-point Likert scale from 1 (“not at all true of me”) to 5 (“extremely true of me”). Responses to each item are summed to calculate a total score, with a potential range of 12–60; higher scores indicate poorer problem-solving ability.

Change in current suicidal ideation at T2 when compared to T1 will be measured using a single purpose-designed item, “Are you thinking about killing yourself right now?”. If yes, participants will be asked to indicate which of the following describes the level of suicidal ideation they are experiencing: “Mild suicidal thoughts with no plan or intent to act”; “Moderate suicidal thoughts with a rough plan and some intent”; “Severe suicidal thoughts with a specific plan and intent to act”. The counts falling into the different levels will be used for analysis.

Change in health service use from formal and informal sources at T2, T3, and T4 when compared to T1 will be assessed using the Resource Use Questionnaire (RUQ) and a purpose-designed measure respectively. The RUQ was adapted from the Young Mind Matters Service Use questionnaire [51] and assesses use of mental health professionals and services, mental health-related hospitalisations, medication use for mental health reasons, and school-based mental health services. These data will also be used for the economic evaluation.

Change in attitudes towards seeking help from adults at school, and attitudes towards overcoming secrecy barriers, at T2, T3, and T4 when compared to T1, will be assessed using scales derived from the previous US Sources of Strength trial [52] and used in the Australian Sources of Strength trial [5]. Items are rated from 1 (strongly disagree) to 4 (strongly agree). Items on these scales are summed, with higher scores reflecting more positive attitudes towards help-seeking from adults at school, or more positive intentions to get help for suicidal friends and resist requests for secrecy.

Change in perceived ability and intention to intervene with a suicidal person at T2, T3, and T4 when compared to T1 will be assessed using the Perceived Behavioural Control and Intention subscales of the Willingness to Intervene Against Suicide Questionnaire (WIS) [53]. The scales have 20 and 22 items respectively. Both are rated on a 5-point scale ranging from 1 (“strongly disagree”) to 5 (“strongly agree”). Items 1, 3, 5, 10, 14, and 16 on the Perceived Behavioural Control subscale and items 12, 18, 19, 20, and 21 of the Intentions subscale are reverse-scored. The potential range of scores is 20–100 and 22–100 respectively; a higher score indicates a higher endorsement of intervening.

Change in stigma towards suicide at T2, T3, and T4 when compared to T1 will be assessed using the Stigma of Suicide Scale (SOSS)—Short Form [54]. This measure contains 16 one- or two-word descriptors of people who die by suicide, and respondents are asked to rate their level of agreement with each item on a 5-point scale ranging from 1 (“strongly disagree”) to 5 (“strongly agree”). The mean response to all items is calculated to score this instrument, with higher mean scores indicating greater suicide stigma.

Change in suicide literacy at T2, T3, and T4 when compared to T1 will be assessed using the Literacy of Suicide Scale (LOSS)—Short Form [55]. This scale contains 12 items rated on a “true/false/don’t know” scale. The correct response for items 1, 3, 4, 5, 7, 8, and 10 is “false” while items 2, 6, 9, 11, and 12 are correctly answered “true”. The scale provides a total literacy score (percent correct) where higher scores indicate greater suicide literacy.

Change in health-related quality of life during the course of the trial (T1, T2, T3, and T4) will be assessed using the Child Health Utility—9 Dimension (CHU9D) [56]. The CHU9D is a multi-attribute utility instrument suitable for young people aged 7–17 years. It comprises a short questionnaire alongside a set of preference weights using general population values. The questionnaire has nine items with five response levels per item and can be used to derive quality-adjusted life years (QALYs) for use in a cost-utility analysis (i.e. the economic evaluation).

#### Additional measures

To characterise the sample at baseline, participants will be administered a standard demographic questionnaire. They will also be asked about any previous mental health diagnoses, exposure to suicide in others, and any previous suicide prevention training undertaken.

At each time point, participants will be asked about their history of suicide planning and attempt, using the four suicide items from the Youth Risk Behaviour Survey (YRBS) [57]. These yes/no items assess if the respondent has had suicidal ideation or made a suicide plan or attempt (and its seriousness) during the past 12 months at baseline, or in the period between assessment points.

Participant views on the safeTALK workshop, including whether or not they thought it was “enjoyable”, “upsetting”, and “worthwhile”, will be assessed at T2 only using seven purpose-designed items. Participant views on the Reframe IT intervention (or for those in the control group, acceptability of *not* receiving Reframe IT) will be assessed using 11 purpose-designed items at T3 only.

Finally, three additional scales will be used that are not directly related to the aims of the present study. First, the Distress Questionnaire—5 (DQ-5) [58] will be administered at T1 to facilitate future comparison of data with another trial of a school-based suicide prevention programme in Australia [5]. The DQ-5 is a 5-item measure of distress, wherein participants are asked to specify on a 5-point scale, from 1 (“never”) to 5 (“always”), how frequently they have experienced certain indicators of distress over the past 30 days. The potential range of scores is 5–25, with higher scores indicating a greater level of distress. Next, two scales will be included as part of a larger study conducted by researchers in Europe examining whether participating in suicide prevention research is associated with distress. The first is the Patient Health Questionnaire—4 item version (PHQ-4) [59], a screener of anxiety and depression symptoms. As two of the items are included in the PHQ-9, only the remaining two items (“how often have you been bothered by feeling nervous, anxious or on edge”; “how often have you been bothered by not being able to stop or control worrying”) will be added to the T1 questionnaire only. The second scale is a purpose-designed 11-item scale to assess experimentally induced distress, which will be administered at T4. It includes two subscales: experimentally induced distress in absolute terms (i.e. participation was distressing) and in relative terms (i.e. participation was more distressing than everyday life events). This scale was adapted from Yeater, Miller, Rinehart, and Nason [60].

### Sample size and power calculation

The critical power calculation for this study relates to Component 2 (RCT of Reframe IT). The primary outcome variable for Reframe IT is reduced suicidal ideation, measured by the SIDAS, at 24 weeks (T4), in comparison to SIDAS scores at Time 2.

The Suicidal Ideation Questionnaire (SIQ) [61, 62] was used in the Reframe IT pilot study [33]. The SIQ and SIDAS are both continuous self-report measures of the frequency of cognitions related to suicide within the past month, with higher scores corresponding to more frequent and severe suicidal ideation. The range of the SIDAS is 0–50 and the range of the SIQ is 0–180. A SIDAS score of 1 or more indicates “risk for suicide”, whereas a SIQ score of 41 or more indicates “need for further evaluation of psychopathology”. As the SIQ licence is too expensive to use on a large scale, the SIDAS is being used in its place. In the absence of pilot data for the SIDAS, the power calculation is based on the SIQ. This can be reasonably justified given the similarities between the measures and their cut-offs and has been calculated in consultation with the study statistician.

In the Reframe IT pilot study, there were three time points of data collection (corresponding to T2, T3, and T4 as labelled in the current study). The mean reduction in SIQ between T1 and T3 (i.e. corresponding to T2 and T4 in the present study) for the pilot control group was 61.6 points (SD = 42.3) and for the pilot intervention group this was 47.1 points (SD = 41.6). The difference between these two reductions was 14.5 points. We also observed an intra-class correlation of 0.023 within schools, which gives a design effect of 1.1. Using these data, and making the conservative assumption that there is no correlation between SIQ scores within individuals over time, a 5% significance level and 80% power means that a sample size of 134 per arm (268 in total) is required.

Based on pilot data, and in consideration of the self-reported nature of the data collected, we estimate that, to recruit the required 268 students, we need to screen 4020 students (see Fig. 1). This is based on 20% drop-out rate among those who are classed as high-risk, consenting, and randomised; 33% of those identified as high-risk consenting to participate in the trial and being randomised (335 consenting and randomised, and analysed on an intention-to-treat basis); and 25% of the total sample endorsing suicidal ideation within the past month (1005 students). There are 141 mainstream secondary schools in the region and approximately 140 year 10 students per school. It is therefore estimated that approximately 29 schools will be recruited in total, although this number may fluctuate depending on the rate of student recruitment. Schools will be recruited in batches throughout the project. If the target sample size is reached before the 29 schools have been recruited, no further schools will be recruited. Similarly, if we recruit the target 29 schools but fail to recruit the required number of participants, more schools will be invited to participate. In the event that we struggle to meet the recruitment target, or if it is unfeasible to recruit year 10 students at a particular school, year 11 students may also be recruited.

**Fig. 1 Fig1:**
[figure not shown]
Sample size calculation based on projected rates of endorsement of suicidal ideation, consent, and attrition

Recruitment numbers will be monitored closely by the study team and the Sponsor. If it becomes apparent that we are not on track to meet our recruitment target, the study team will meet to discuss alternative recruitment measures. Recruitment rate success will be formally assessed every 6 months. The relevant ethics committees will be notified in the case of any proposed amendments to the protocol.

### Randomisation and treatment allocation

Students who consent to participate in Component 2 will be randomised to the intervention group (Reframe IT plus TAU) or to the control group (TAU only) using block randomisation with varying block sizes and stratified by school. The allocation ratio will be 1:1. The randomisation schedule is computer generated by independent Information Technology (IT) personnel with guidance from the study statistician. The schedule will then be implemented by a member of the study team (other than the statistician) into the REDCap database management software for allocating treatments to individual students.

A member of the study team will inform school wellbeing staff of the outcome of randomisation, and they will then inform students. With the exception of the study statistician, study team members are not blind to the treatment allocations. The study statistician will not have access to the randomisation component of the database and will not be told about the treatment allocations, and will therefore remain blinded. As the study statistician will not be involved in any aspect of this study operations other than data analysis, there are no circumstances we could foresee under which the study statistician would be required to be unblinded.

### Statistical analyses

#### Component 1

For each continuous outcome, changes over time will be assessed using linear mixed effects modelling with school included as a random factor. This analysis will examine whether there is a trend over time and whether the trend is linear or non-linear. Change in current suicidal ideation between T1 and T2 will be assessed using the McNemar–Bowker symmetry test for nominal data.

#### Component 2

Descriptive statistics will be used to compare participant characteristics between the study arms, and to assess for any imbalance.

The analysis will adopt the intention-to-treat approach, which is to include in the analysis all participants who have been randomised and regard each participant as belonging to the randomised group concerned irrespective of protocol adherence. Difference in change in the primary outcome of SIDAS score between the treatment groups will be examined using linear mixed effects modelling with the treatment group as a fixed factor and school included as a random factor. Secondary outcome measures will be similarly analysed. As a secondary analysis, compliance (as measured by the number of modules completed) and other potential covariates (e.g. gender) will be accounted for.

If the amount of missing data is non-trivial, multiple imputation will be considered to handle the missing data.

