### Procedure

Participants will be assessed at four time-points: baseline (T1), 2 weeks post-baseline (T2), 12 weeks post-baseline (T3), and 24 weeks post-baseline (T4). The T2 assessment will be completed immediately following participation in the safeTALK workshops, and T3 at the end of the Reframe IT intervention period (see Table 1).

**Table 1 Tab1:** Schedule of assessments and interventions

Time point		Study period				
	− T1	T1	T2		T3	T4
		Baseline Week 1	Week 3	Weeks 4–12	Week 12	Week 24

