### Outcomes and measures

#### Primary outcome

The primary outcome for this study is change in past 4-week suicidal ideation at T3 and T4 when compared to T2, assessed via the SIDAS [45]. The SIDAS is designed to screen individuals in the community for presence of suicidal thoughts and assess the severity of these thoughts. It comprises five items, each targeting an attribute of suicidal thoughts: frequency, controllability, closeness to attempt, level of distress associated with the thoughts and impact on daily functioning. Responses are measured on a 10-point scale. Total SIDAS scores are calculated as the sum of the five items, with controllability reverse scored (10 = 0, 9 = 1,…, 0 = 10), with total scale scores ranging from 0 to 50. Items are coded so that a higher total score reflects more severe suicidal thoughts.

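### The ordered current-ideation item, the direct check for immediate harm from the workshop, gets a valid but non-directional nominal test; and the Component 1 model, if fitted as worded, omits the student level

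*Protocol article*

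**What the plan says.** All references are to the protocol article.

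- **Current ideation.** Secondary outcomes describes a single yes/no item on present suicidal thoughts. A yes leads to three grades defined by increasing plan and intent, and the counts per level are to be analysed. Statistical analyses, Component 1, states: "Change in current suicidal ideation between T1 and T2 will be assessed using the McNemar–Bowker symmetry test for nominal data".
- **Continuous Component 1 outcomes.** The same section says "changes over time will be assessed using linear mixed effects modelling with school included as a random factor", and adds: "This analysis will examine whether there is a trend over time and whether the trend is linear or non-linear". Secondary outcomes defines stigma, literacy, willingness to intervene and help-seeking attitudes as change at T2, T3 and T4, each against T1.
- **Repeated measurement.** Procedure: "Participants will be assessed at four time-points".
- **Component 2.** The difference in change is examined by "linear mixed effects modelling with the treatment group as a fixed factor and school included as a random factor". The primary outcome is "change in past 4-week suicidal ideation at T3 and T4 when compared to T2, assessed via the SIDAS", while Sample size and power calculation names T4 against T2 alone.
- **Safety hypothesis.** Aims and hypotheses expects the programme to have no iatrogenic effects.

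**The concern.** The ideation item has a natural order, and the harm question has a direction: do more students move to a worse level than to a better one across the workshop? McNemar–Bowker asks only whether any pair of levels is asymmetric in either direction. With four levels there are 4 × 3 / 2 = 6 pairs, so a consistent shift towards worse levels is spread over up to 6 degrees of freedom. Because absence of harm is the expected result, a test with little power makes that result easier to obtain.

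The item is hard to replace. T2 is completed straight after the workshop and two weeks after baseline, while the SIDAS looks back four weeks, so the T2 SIDAS score mostly describes the period before the workshop.

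The second matter is the Component 1 mixed model. Each student can contribute four scores, yet the only clustering level named is the school. A model with no student-level term treats one student's scores as independent given school, and the precision of change over time is then misjudged.

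**Working it through.** **1. Power of the ideation test.** The document gives no rates for this item, so the rates here are assumptions.

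Inputs: n = 4020 students to be screened (Sample size and power calculation); two-sided 5% level; assumed improving rates over the six pairs of 1.2%, 0.3%, 0.1%, 0.3%, 0.1% and 0.1%, total 2.1%; worsening more frequent by the same factor f in every pair.

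With w worsening and b improving, the noncentrality is λ = n(w − b)² / (w + b). When f is the same in all pairs, summing this over the pairs for McNemar–Bowker gives the same λ as the 1-df comparison. For f = 1.5, w = 0.0315 and b = 0.021:

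λ = 4020 × 0.0105² / 0.0525 = 8.44.

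The noncentral chi-square distribution then gives power 0.83 on 1 df and 0.56 on 6 df. Simulation with 20,000 replicates agrees:

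| n | f | McNemar–Bowker | Worse vs better (1 df) | Ordered score |
|---|---|---|---|---|
| 4020 | 1.0 (null) | 4.2% | 5.0% | 5.0% |
| 4020 | 1.3 | 21% | 44% | 39% |
| 4020 | 1.5 | 56% | 83% | 77% |
| 4020 | 1.7 | 86% | 98% | 95% |
| 2000 | 1.5 | 26% | 54% | 47% |

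More generally, a λ that gives 80% power on 1 df (7.85) gives 52% on 6 df. If sparse pairs drop out and 3 df remain, it gives 64%.

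Sensitivity to the pattern: put the whole excess of 1.05 percentage points into the none-to-mild pair. That pair then has w = 0.0225 and b = 0.012, so Bowker's λ rises to 4020 × 0.0105² / 0.0345 = 12.85 and its power to 77%. The 1-df test stays at 83%.

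**2. Component 1 standard errors if school is the only random factor.** Assume equal within-student correlation ρ across visits; the document gives no value for the analysis. The true variance of a within-student time contrast is proportional to 1 − ρ. A model without a student term puts student variance into the residual and uses approximately 1. Hence the ratio of model SE to true SE is about 1/√(1 − ρ), the actual type I error is 2(1 − Φ(1.96 × ratio)), and a test meant to have 80% power keeps Φ(2.80/ratio − 1.96).

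| ρ | SE ratio | Actual type I error | Power kept |
|---|---|---|---|
| 0.3 | 1.20 | 1.9% | 65% |
| 0.5 | 1.41 | 0.6% | 51% |
| 0.7 | 1.83 | 0.03% | 34% |

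Fitted mixed models on simulated data (29 schools, four visits, 150 replicates, school intercept only) gave ratios of 1.13, 1.30 and 1.62. These are noisy at 150 replicates and somewhat below the formula, but in the same direction: the standard errors are too large.

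**3. Component 2.** With one change score per student, such as T4 minus T2, there is a single record per student. A school random effect then needs no student term beside it, and the standard error is unaffected.

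**The case against.** **The article does not say that school is the only random factor.** A condensed article often leaves the covariance structure to the full protocol or SAP. This stands, and it makes the standard-error point conditional on the model being fitted as worded. A reader might infer that the planned standard errors are wrong; the text does not establish that.

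**McNemar–Bowker is a valid test.** This stands. It keeps its size (4.2% above), affects no standard error and is inefficient rather than wrong. Its disadvantage also narrows when worsening is confined to one pair of levels (77% against 83%), and 6 df is a maximum.

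**Harm is watched in other ways.** Individual ideation triggers the safety protocol at every time-point, and adverse events are recorded and assessed for causality. That protects students but does not estimate a group-level shift. The counts would show a direction, but without a test or an interval for it. It is also true that an uncontrolled before-and-after series cannot attribute a shift to the workshop, whichever test is used.

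**Two stronger readings are not supported.**

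- A reader might infer that the Component 2 primary test is anti-conservative. If the T3 and T4 changes, which share T2, were stacked with correlation 0.5 and no student term, type I error would be 2(1 − Φ(1.96/√1.5)) = 11%. The article describes no such stacking, and its sample-size section points to one T4-minus-T2 change per student.
- A reader might infer that a gain at T2 that later fades would be missed by a trend analysis. The plan also examines whether the trend is non-linear, which largely meets this. What remains is that the defined contrasts against T1 are not named in the analysis.

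**Conclusion.** The firm part is the ideation test, because it rests on what the article states: a graded item is assigned a nominal omnibus test. The loss is power, about 56% against 83% under the assumed rates at f = 1.5. It ranges from 21% against 44% at f = 1.3 to 86% against 98% at f = 1.7, and shrinks if the change is concentrated in few pairs. It matters because it favours the conclusion of no harm.

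The conditional part is the Component 1 model. If it is fitted with school as the only random factor, standard errors for change over time are too large by about 1.2 to 1.8 times at assumed correlations of 0.3 to 0.7. The error is conservative: real change would be reported with too little certainty.

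Nothing here shows a fault in the Component 2 type I error. The 11% is a property of one possible implementation, not of the plan.

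**What to change.** 1. Analyse current ideation at T1 and T2 as ordered and directional, by a sign or signed-rank test or an ordinal mixed model. Report percent worsened minus percent improved with a confidence interval. Under the f = 1.5 assumptions this would read 3.15% − 2.10% = 1.05 points, with SE √((0.0525 − 0.0105²)/4020) = 0.36 points and a 95% interval of about 0.3 to 1.8 points before any allowance for school clustering. McNemar–Bowker can stay as a supporting analysis.
2. For Component 1, state a student random effect within school, or an unstructured within-student covariance. Name contrasts of T2, T3 and T4 against T1, to match the outcome definitions.
3. For Component 2, say whether T3 and T4 are modelled separately or jointly. Only a joint model needs a student-level term and treatment-by-time.

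The cost is analysis wording, with no new data and no change in sample size. The one small loss is that a directional test is less sensitive to changes that cancel, such as some levels worsening while others improve.

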### Aims and hypotheses

This project aims to evaluate the effectiveness of an integrated programme comprising universal, selective, and indicated components in reducing suicide risk, improving risk recognition, and increasing health service use among young people across North West Melbourne. Secondary aims are to evaluate the programme’s safety and cost-effectiveness. The programme involves the delivery and evaluation of universal educational workshops (safeTALK) to school students plus screening students for suicide risk (universal and selective approaches; Component 1), and the evaluation of online CBT (Reframe IT) delivered to students identified as being at risk (indicated approach; Component 2). Several hypotheses have been generated relating to each of the project components as well as the project as a whole.

It is hypothesised that completion of the safeTALK workshop will be associated with increased intentions to intervene with a suicidal person, higher levels of suicide literacy, higher levels of perceived behavioural control regarding intervening with a suicidal person, and reduced stigma towards suicide and suicidal behaviour.

It is hypothesised that the screening will lead to the identification of students at risk of suicide-related behaviour who had not previously sought help.

It is hypothesised that, compared to the control group, students in the Reframe IT intervention group will demonstrate reduced suicidal ideation, reduced symptoms of depression, reduced hopelessness, and improved problem-solving.

It is hypothesised that the project as a whole will lead to increased health-service use; increased help-seeking from informal sources; and improved attitudes towards help-seeking.

Finally, it is hypothesised that the programme will be cost-effective and have no iatrogenic effects.

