## Methods

### Study design

The present study will adopt two methodological approaches: Component 1 will employ a single-group, pre-test/post-test case series; Component 2 is a parallel superiority randomised controlled design, where the intervention condition (Reframe IT plus treatment as usual; TAU) is compared to TAU. Component 2 will be conducted and reported according to the Consolidated Standards of Reporting Trials (CONSORT) statement [36].

The study was designed to be conducted over a 5-year period (2019–2023), with a 3-year intervention phase. There has, however, been a 1-year suspension due to the COVID-19 pandemic during 2020, meaning that the study will continue into 2024.

The study is registered with the Australian New Zealand Clinical Trials Registry (ID: ACTRN12621000770864). This is the primary registry of the WHO ICTRP network. It includes all items from the WHO Trial Registration data set, available at https://www.anzctr.org.au/Trial/Registration/TrialReview.aspx?id=381921&isClinicalTrial=False. It received ethical approval from the University of Melbourne Human Research Ethics Committee (HREC; ID 1852317) and the Department of Education Victoria Research Ethics Committee (ID 2019_003951) [see Additional files 2 and 3].

This protocol is reported in line with the Standard Protocol Items: Recommendations for Interventional Trials (SPIRIT) 2013 statement [37, 38] [see Additional file 4 for checklist].

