#### Screening for risk

The screening will take the form of self-report measures embedded into the questionnaires at each time point. Students who report suicidal ideation within the past 4 weeks (SIDAS score of 1 or higher) or any level of current suicidal ideation (single multiple-choice item) will be contacted by a member of the school wellbeing team or the research team, who will assess risk and refer them to appropriate support.

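### The symmetry test named for T1–T2 change in current suicidal ideation cannot support the hypothesis of no iatrogenic effects; onset, remission and net change need estimates with school-clustered intervals

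*Protocol article*

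**What the plan says.** All references are to the protocol article.

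- **Aims and hypotheses:** "Secondary aims are to evaluate the programme’s safety and cost-effectiveness". The last hypothesis reads "Finally, it is hypothesised that the programme will be cost-effective and have no iatrogenic effects".
- **Secondary outcomes:** "Change in current suicidal ideation at T2 when compared to T1 will be measured using a single purpose-designed item". Students who answer yes choose mild, moderate or severe, and "The counts falling into the different levels will be used for analysis". With 'no' as the lowest level, this is a paired table of four ordered levels.
- **Statistical analyses, Component 1:** "Change in current suicidal ideation between T1 and T2 will be assessed using the McNemar–Bowker symmetry test for nominal data". Continuous outcomes in the same component get a mixed model with school as a random factor.
- **Study design:** "Component 1 will employ a single-group, pre-test/post-test case series".
- **Procedure:** T2 comes two weeks after baseline, directly after the safeTALK workshop.
- **Screening for risk:** students who report past-month or current ideation "will be contacted by a member of the school wellbeing team or the research team, who will assess risk and refer them to appropriate support".

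**The concern.** The hypothesis is one of absence, whereas the null of the named test is that, for each pair of levels, as many students move one way as the other. Failing to reject that null does not show that harm is absent. Four features of the test make it a poor fit for the safety aim.

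1. It has no direction, so a significant result alone does not separate harm from benefit.
2. It treats the levels as nominal although they are ordered, and with four levels it spends up to 6 degrees of freedom.
3. It takes no account of school, although the component's continuous outcomes are modelled with school as a random factor.
4. It compares two flows that can have different causes. New onset at T2 is the harm signal for screening and safeTALK. Remission may be raised by the contact and referral that follow a positive screen. Equal flows cancel, however many new cases there are.

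The Discussion ties wider use in schools to the programme being found efficacious, safe and cost-effective, so the basis of any safety statement matters.

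**Working it through.** **Sample size available.** Sample size and power calculation gives 4020 students to be screened. This reproduces: 268/0.80 = 335; 335 × 3 = 1005 (one third consenting); 1005/0.25 = 4020. Taking 33% literally gives 335/0.33/0.25 ≈ 4061. Loss between T1 and T2 is ignored below, so 4020 is a best case.

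**Assumptions.** The article gives no rate of current ideation; its 25% is for the past month. I assume T1 prevalence of 2%, 5% or 10%, half of these students remitting by T2, and onset equal to remission when there is no harm.

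**Cancellation.** The Bowker statistic is the sum over pairs of levels of (n_ij − n_ji)²/(n_ij + n_ji). With 60 students moving from none to mild/moderate/severe as 40/15/5, and 60 moving back in the same pattern, every term is 0 and p = 1.00. Yet there are 60 new cases, 60/4020 = 1.5% of the sample.

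**Excess that stays non-significant against 60 remissions.**
- Yes/no McNemar with 83 onsets: (83 − 60)²/(83 + 60) = 529/143 = 3.70, p = 0.054. With 84 onsets: 576/144 = 4.00, p = 0.046.
- Four-level Bowker with 102 onsets (62/27/13) against 60 remissions (40/15/5), other pairs populated and symmetric: 22²/102 + 12²/42 + 8²/18 = 4.75 + 3.43 + 3.56 = 11.73 on 6 df, p = 0.068. Collapsed to yes/no, the same data give 42²/162 = 10.89, p = 0.001. The net rise is 42/4020 = 1.04 percentage points.

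**Chance of missing a 30% rise in onset, yes/no McNemar.** With r remissions and o = 1.3r onsets, expected z = (o − r)/√(o + r), and the chance of missing is about Φ(1.96 − z).

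| T1 prevalence | r | o | extra cases | z | missed |
|---|---|---|---|---|---|
| 2% | 40.2 | 52.3 | 12 | 1.25 | 76% |
| 5% | 100.5 | 130.7 | 30 | 1.98 | 49% |
| 10% | 201 | 261.3 | 60 | 2.80 | 20% |

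**What separate reporting shows.** At 5% prevalence, 4020 − 201 = 3819 students have no current ideation at T1. Without harm, onset is 100.5/3819 = 2.6%. If onset and remission both rise by 30%, onset becomes 130.7/3819 = 3.4%, while net change stays at 0 and the symmetry test sees nothing.

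**Precision of net change at 5% prevalence, no true change.** The discordant share is (100.5 + 100.5)/4020 = 0.05. The one-sided 95% upper limit is 1.645 × √(0.05 × deff/4020).
- No clustering (deff = 1): 0.58 percentage points.
- With the article's ICC of 0.023 and 4020/29 ≈ 139 students per school: deff = 1 + 138 × 0.023 ≈ 4.2, and the limit is about 1.2 points. That ICC comes from the pilot SIQ data, so applying it here is an assumption.

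**The case against.** **The link is inferred.** A reader might infer that the authors will report p > 0.05 as proof of safety. The article says only that change will be assessed with this test, and McNemar–Bowker is a standard test of paired categorical change. This stands, so the point is limited to what the test can support. Even so, T1–T2 change in current ideation matches no efficacy hypothesis in the article, and no other analysis of ideation is named for that window.

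**This is not the only safety information.** A reader might also infer that the whole safety case rests on this test. It does not. Adverse and serious adverse events are recorded with a causality judgement, a Safety Monitoring Committee meets quarterly, and study discontinuation criteria cover attempts and deaths. YRBS suicide items are asked at every time point, and a safeTALK item asks whether it was upsetting. These sources stand, but the article names no analysis of them that estimates change in ideation across the cohort.

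**A pass/fail margin on net change.** This is tempting, but net change is onsets minus remissions, so it cancels in the same way. With limits of 0.6 to 1.2 points against a 30% rise worth 30/4020 = 0.75 points, such a rule could often fail with no harm present. The documents do not support requiring one.

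**The figures rest on assumptions.** Prevalence, remission, level split and size of harm are all assumed. The 6-df result also needs the mild, moderate and severe pairs to be populated; if they were empty and 3 df applied, 11.73 would pass the 1% point of 11.34. I therefore give no general miss rate for the Bowker test.

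**Detail left to an analysis plan.** Intervals and tables often sit there, and the paired counts already contain onset and remission. But the protocol itself fixes the test, and that choice is the point here. Referral effects by T2 are plausible but unquantified, since Screening for risk sets no time for contact.

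**Conclusion.** The point holds as a mismatch between a stated safety hypothesis and the analysis named for the one ideation outcome spanning screening and safeTALK. A non-significant McNemar–Bowker result cannot support absence of iatrogenic effects, and a significant one does not by itself show direction.

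Under the assumed rates, a 30% rise in onset is missed about half the time at 5% prevalence even by the simpler yes/no test, with a range of 76% to 20% for prevalence of 2% to 10%. These figures illustrate scale and do not predict this trial's results. That matched flows cancel, and that the test has no direction, does not depend on them.

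The documents do not show that the authors intend to equate p > 0.05 with safety, or that safety rests on this test alone. Without a control group, no analysis of Component 1 can attribute onset or remission to the programme.

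**What to change.** In Statistical analyses, Component 1, report the following for current suicidal ideation at T2 against T1, each with a confidence interval that allows for clustering by school:

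- (a) new onset among students without current ideation at T1, and worsening among those at a lower level at T1;
- (b) remission or improvement;
- (c) net change in the proportion with any current ideation.

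Base the safety statement on these intervals, above all the upper limits for onset and net change, and read it alongside the adverse-event and YRBS information. Keep McNemar–Bowker as a supportive test. State that p > 0.05 on it is not evidence of safety, and that neither flow can be attributed to the programme without a control group.

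The cost is a little more analysis of data already collected, and a more cautious safety statement. At 5% prevalence, the upper limit for net change would be about 0.6 percentage points without clustering, and up to about 1.2 if the stated ICC applies.
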